**Phase 1**

Aim 1: These small group meetings will be held virtually using a KP IT approved application.

Aim 2: The workflow will be developed under the direction of the PIs at SSF and DOR.

**Phase 2**

Aim 3: The HC APM will be based in SSF; data analysis will be conducted at the Division of Research.

If this is a multi-site study:

- Specify what procedures are being performed at this site or by this site's personnel (consider recruitment, consent process, study procedures, information/biospecimen analysis, etc.).

N/A

- State how each site will satisfy its IRB review requirements. Indicate if you are asking this site's IRB to rely on another IRB or if another institution would like to rely on this site's IRB and include this information in the eIRB Initial Project submission

N/A

For research conducted outside this site describe: (Community, Reservations etc.)

- Describe site-specific regulations or customs affecting the research at that location.

N/A

- Local scientific and ethical review structure outside this site.

N/A

**6. Recruitment Methods**

Describe how study participants will be recruited and enrolled.

**Phase 2**

There will be no recruitment. All patients will already be receiving usual care from an APM.

- For study participants, the HC will communicate with each participant's provider (usual APM or physician) to coordinate care; the study participant will receive proactive intervention by the HC as an augmentation to their usual care.
- For the data-only patients, there will be no contact.

Indicate whether you will openly recruit using advertisements, websites, flyer, or brochures. (Upload the final versions of all recruitment materials to your submission to the IRB.)

N/A

Indicate if you plan to do targeted recruitment using existing records or referral. Please submit final versions of all referral emails/scripts.

N/A

Describe, by position/title, who will be recruiting and enrolling participants (providing the specific names of research team members is not necessary).

**Phase 2**

Participants will be enrolled by the Hypoglycemia Champion who will be a pharmacist APM.

Describe any plans for the participants in the currently proposed study to be re-contacted or recruited for future follow-up studies. (Note that participants should be informed of this potential for re-recruitment or future follow-up studies during the current study's consent process.)

None.

Please note the following KPNC IRB guidelines:

- Contact of prospective subjects will be limited to three (3) attempts in one week, for no longer than three (3) continuous weeks.
- Messages left will be limited to one (1) per week for no more than three (3) weeks.
- No more than two (2) recruitment mailings (email, flyer, brochure, etc.).
- If permission from the patient's PCP is necessary to contact the patient:
  - If PCP does not respond to request, recruitment attempts (phone, mailings, etc.) may not begin until 2 weeks after the PCP's permission was requested.
  - If PCP grants permission, recruitment attempts may begin with no waiting period.

**7. Informed Consent Process****a. Written Consent**

Describe how you will obtain and document consent, including:

**Phase 2**

A waiver of written informed consent is requested.

- Where, when and how the consent process will take place.

N/A

- How the research team will ensure that subjects have sufficient time to consider whether to participate in the research

N/A

- A process to ensure ongoing consent.

N/A

- Steps that will be taken to minimize the possibility of coercion or undue influence.

N/A

- Any steps that will be taken to ensure the subjects' understanding.

N/A

- If you are planning to conduct remote informed consent, please describe the process in detail, including any electronic platforms. Indicate how the consent process will be documented.

N/A

NOTE: For each federally-supported clinical trial, one IRB-approved informed consent form used to enroll subjects must be posted by the awardee or sponsor conducting the trial on a publicly available Federal website that will be established as a repository for such informed consent forms.

b. Waiver of Informed Consent

Provide rationale and justification for the Waiver of Informed Consent for this study, including:

- Explain how the proposed research presents no more than minimal risk to the study participants.

**Phase 2**

Study participants will receive augmented usual care from the HC APM (whose goal is to fully implement the new standard of care protocol with the intention of reducing the risk of hypoglycemia and improving safety). The attention presents no more than minimal risk to participants. (Data-only patients are not research subjects; they will receive usual care from their regular APM; the study will have no direct contact with the data-only patients.)

- Explain how the waiver of informed consent will not adversely affect the rights and welfare of the participants.

**Phase 2**

Receiving usual care with proactive attention from the HC APM will not affect the rights and welfare of participants.

- Explain why this research cannot practically be carried out without a waiver of informed consent. Note: research regulations require that justification for a waiver of consent explain why it is impracticable to perform the research, and not just impracticable to obtain consent. Practicability cannot be determined solely by considerations of convenience/cost/speed.

**Phase 2**

Receipt of usual care does not require obtaining consent at every step of every encounter. To introduce a consent requirement into the APM encounter would be inappropriate.

- If the research involves using identifiable private information or identifiable biospecimens, provide justification for why the research cannot practicably be carried out using deidentified information.

**Phase 2 )** The research could not be practicably carried out using de-identified information or data because linking the data extracted from the sources requires a common identifier to link the data.

- Assess whether it is appropriate to provide the subjects with additional pertinent information after participation.

**Phase 2**

In the course of usual care, patients are provided with pertinent information about their care and care options.

**c. Waiver of Signed (Documented) Informed Consent**

Provide rationale and justification for the Waiver of Signed (Documented) Informed Consent by identifying which of these three conditions applies and justification for how the criteria is met.

- 1) The research involves no more than minimal risk to participants AND involves no procedures for which written consent is normally required outside of the research context.

**Phase 2**

Participants will receive augmented usual care from the HC APM (whose goal is to fully implement the new standard of care protocol) which does not normally require written consent.

- 2) The signed consent form would be the only record linking the participants to the research, and the principal risk to participants would be potential harm resulting from a breach of confidentiality.

N/A

- 3) The subjects or legally authorized representatives are members of a distinct cultural group or community in which signing forms is not the norm.
  - a. Describe the distinct cultural group or community
  - b. Describe why signing forms is not the norm
  - c. Explain how the research presents no more than minimal risk of harm to these subjects
  - d. Provide an appropriate alternative mechanism for documenting that informed consent is obtained

N/A

**d. Alteration of Informed Consent**

Identify the required elements of informed consent that you wish to remove or alter.

N/A

Provide justification for their removal or alteration.

N/A

**e. Non-English-Speaking Subjects**

If subjects who do not speak English will be enrolled, describe how the consent discussion will take place and indicate if translated consent forms or short forms will be used. Confirm that an interpreter will assist with the initial consent process and subsequent study visits.

All contact with non-English-Speaking patients will utilize interpreters, in accordance with the usual clinical workflows when care is provided to these patients. As previously noted, a waiver of signed consent is requested, since this is not different from usual clinical care.

IMPORTANT NOTE: Please be aware that if it is expected that you will enroll non-English speakers in the study, short forms should not be used as the only Consent option for these individuals, they should only be used if a non-English speaking participant is unexpectedly encountered. However, the possibility of encountering non-English speaking potential subjects in the Bay Area is a possibility and this possibility should be considered, and budgeted for, when preparing the initial study submission for IRB review.

f. Assent of Children and Parent Permission

IMPORTANT NOTE: Child Consent may be obtained in certain situations (for example, conducting family planning or sexually transmitted disease (STD) research). In addition, for older children ages 16 and up who participate in an adult study, the consent document can be used in place of the assent document.

Describe how you will obtain and document assent/parental permission, including:

- Describe your plan for obtaining parent permission. The permission of one parent is generally sufficient for minimal risk research, or for greater than minimal risk research if there is the potential for direct benefit to the child. For studies involving greater than minimal risk with no prospect of direct benefit to the child, permission of both parents is required unless one parent is deceased, unknown, incompetent, or not reasonably available, or when only one parent has legal responsibility for the care and custody of the child.

N/A Children will not be enrolled.

- Describe whether permission will be obtained from individuals other than parents, and if so, who will be allowed to provide permission.

N/A

- Indicate whether assent will be obtained and documented from all, some, or none of the children.

N/A

- If assent will only be obtained from some children (because of very young age, severe cognitive impairment, etc.), indicate which children will be required to assent and which will not.

N/A

- When assent of children is obtained, describe whether and how it will be documented.

N/A

- When subjects might reach the age of majority during the study, describe the plan to obtain consent from these subjects at that time using an adult consent form.

N/A

g. Secondary Research for Which Consent is Not Required:

Note: Research involving the use of identifiable biospecimens does not apply to this section.

Note: Although consent may not be required, justification for a waiver of HIPAA Privacy Authorization may still be required.

Secondary Research of identifiable private information or identifiable biospecimens may not require informed consent if at least one of the criteria listed below is met. Select at least one of the following criteria and provide a rationale for how the criteria is met:

- Use of publicly available identifiable private information or identifiable biospecimens.

N/A

- The information and/or biospecimens are recorded by the investigator in such a way that the identity of the subjects cannot be readily ascertained, and the investigator will neither contact the subjects nor re-identify subjects.

N/A

- The research involves only information collection (i.e., no biospecimen collection) and the analysis of this identifiable health information is regulated by HIPAA.

Data will be collected on data-only matched controls (receiving usual care subsequent to the regionwide dissemination of HOAP).

**8. HIPAA Privacy Rule Authorization**a. Written HIPAA Privacy Rule Authorization:

Describe the plan to obtain a signed Privacy Rule Authorization from each subject.

**Phase 2**

A waiver of HIPAA authorization is requested.

b. Waiver of HIPAA Privacy Rule Authorization

If you will not obtain a signed HIPAA Privacy Rule Authorization or if you want to eliminate any required language from the authorization, provide the following rationale and justification.

- Explain why the research could not practicably be conducted without the waiver. Note: research regulations require that justification for a waiver of HIPAA Authorization explain why it is impracticable to perform the *research*, and not just impracticable to obtain HIPAA Authorization. Practicability cannot be determined solely by considerations of convenience/cost/speed.

Receipt of usual care does not require obtaining HIPAA Privacy Rule Authorization at every step of every encounter. To introduce a consent requirement into the APM encounter would be inappropriate.

- Explain why access to and use of the PHI is necessary for the research.

It is necessary to access PHI to assemble the cohort of study participants and data-only patients. Without access to and use of the necessary PHI the research cannot be conducted. Direct contact with study participants is necessary for usual care as well as for this activity.

- Explain why the use or disclosure of PHI for the research poses no more than minimal risk to the subjects' privacy.

Use of PHI poses no more than minimal risk as this study will store PHI in password protected or encrypted electronic files and stored on protected KP servers within each region and within KP networks secured by firewalls. Passwords will not be disclosed to any party not involved in the study, including study teams outside of the KP NCAL region. Patient identifiers will not appear in any part of the publications. When it is necessary to share PHI information among study parties within each respective KP region, password-protected/encrypted files will be transmitted through encrypted KP email or secure file transfer. For all these reasons the use and disclosure of PHI poses no more than minimal risk to the subjects' privacy.

- Provide an adequate plan to protect the PHI from improper use or disclosure.

This study will store PHI in password protected or encrypted electronic files and stored on protected KP servers within KP network secured by firewalls. Passwords will not be disclosed to any party not involved in the study outside of each region. Patient identifiers will not appear in any part of the publications. When it is necessary to share PHI information among study parties within the immediate KP regional team, password-protected/encrypted files will be transmitted through encrypted KP email or secure file transfer. Only designated trained study staff within each regional study team will have access to all data collected as part of this study.

- Provide a plan to destroy identifiers at the earliest opportunity consistent with the purpose of the research.

Personal identifiers associated with participants will be destroyed as soon as possible after the study has finished and after publication of all manuscripts. Since manuscript submission and revision process often requires re-access of patient information, patient identifiers will be kept until all publications generated from the study have been finished, at which time all patient identifiers will be destroyed at the close of the study.

### **c. HIPAA Disclosure Accounting**

The Health Insurance Portability and Accountability Act (HIPAA) Privacy Rule gives patients the right to receive a listing, known as an accounting of disclosure, of their information that is disclosed to others for reasons other than treatment, payment, or health care operations. KP must account for all known disclosures of protected health information for research purposes without the individual's authorization (a waiver or alteration of HIPAA Authorization) both within a KP region (between a Permanente Medical Group, Kaiser Foundation Hospitals, and a Kaiser Foundation Health Plan) and outside of KP.

**Protocol Template  
(Use with Core Data Form)**

KP NCAL IRB Version: 09/14/2021

- What type of PHI is being disclosed?
  - ☒ Clinical/Diagnostic
  - ☒ Demographics
  - ☒ Healthcare
- How many participants are expected to be enrolled in this study at your region?
  - ☐ 49 or less individuals

The investigator should maintain an individual accounting record of all Disclosures made by the research team that are subject to the HIPAA tracking requirements. The investigator must also transmit this tracking information within 20 days of Disclosure to the Regional Compliance Officer. Using: Health Connect Quick Disclosure or Complete the Disclosure of PHI about a single individual for a research purpose Form.

- ☒ 50 or more individuals

If 50 or more individuals, please provide the information for each entity that sponsored the research where PHI is being disclosed. *Please note: If you are disclosing PHI to more than one entity, the following is needed for each entity.*

- **Name**  
KPNC Region
- **Address**  
[name]
- **[contact]

If disclosing PHI to more than one entity, please continue entering the required information below:  
PHI will not be disclosed outside of the KP NCAL entity.

**9. Study Procedures****a. Description**

Describe and explain the study design, including:

- A detailed chronological description of all research procedures.

**Phase 1:****Aim 1**

Months 1-4: Meetings with stakeholders will be convened by PIs.

Months 4-6: Finalize and disseminate “Hypoglycemia on a Page” (HOAP) (such as dissemination at all regional meetings with APMs, “steal this talk” presentations for PCPs, and electronic posting in the Clinical Library).

**Aim 2**

Months 2-4: Workflow/clinical pathway will be developed by PIs.

**Phase 2**Aim 3

Months 5-6:

- Develop procedures and metrics for outcome evaluation
- Identify eligible patients (N=200)(have a high hypoglycemia risk score or a recent ED visit or hospitalization for hypoglycemia); randomly select study participants and data-only patients (matched sample)
- Collect baseline EMR data on study participants and data-only patients

Months 7-12:

- HC APM conducts outreach to study participants for assessment and evaluation; provides hypoglycemia intervention to study participants.

Months 13-21

- Collect outcome data from EMR for study participants and data-only patients.

Months 21-24

- Analyze data and draft manuscript

- Procedures to monitor subjects for safety, including who will review the data and at what frequency for safety issues.

**Phase 2**

APM will routinely monitor study participants for safety and report any concerns to the Investigator.

- Procedures performed to lessen the probability or magnitude of risks.

**Phase 2**

Usual care has no more than minimal risk.

- The source records that will be used to collect information about subjects. (Attach all surveys, scripts, and data collection forms.)

**Phase 2**

Data will be collected from EMR.

- What information and/or biospecimens will be collected including during long-term follow-up.

*Please note, if biospecimens being collected are being used to develop an investigational in vitro diagnostic device, an IDE for the device may be needed. Please review the IVD Device FAQs in IRBNet for guidance.*

**Phase 2**

Data collected from study participants and data-only patients

- Prescribing orders and pharmacy dispensing of medications including
- Durable medical equipment orders and dispensing of continuous glucose monitor devices and supplies
- Relevant lab results (e.g., HbA1c)
- ED visits or hospital admissions for hypoglycemia
- Hypoglycemia on the problem list
- Visit notes

- The duration of an individual subject's participation in the study.

**Phase 2**

Participation in the study will end within 25 months after enrollment of first participant and no later than 01/31/2026.

- The duration anticipated to enroll all study subjects.

Enrollment is expected to end by 01/31/2026.

- The estimated date for the investigators to complete this study (complete primary analyses)  
NOTE: It should be clear exactly which procedures will be conducted for the research as opposed to procedures the subjects would undergo (in the exact manner described in the protocol) even if they were not participating in the study.

The study is expected to be completed by 01/31/2026.

- Describe procedures that will be followed when subjects withdraw from the research, including withdrawal from intervention but continued information and/or biospecimen collection.

Participants who become non-adherent to care provided by HC APM will be followed up per the intent to treat analysis plan.

- Describe any anticipated circumstances under which subjects could be withdrawn from the research without their consent.

Discontinuation of Kaiser membership.

- Describe any procedures for orderly termination.

N/A

- If the study involves genetic testing or collection of genetic information, describe this.

N/A

- Clarify whether research involving biospecimens will (if known) or might include whole genome sequencing (i.e., sequencing of a human germline or somatic specimen with the intent to generate the genome or exome sequence of that specimen).

N/A

- Does the study include basic and clinical research involving recombinant or synthetic nucleic acid molecules, including the creation and use of organisms and viruses containing recombinant or synthetic nucleic acid molecules, and is subject to NIH guidelines (Guidelines: <https://osp.od.nih.gov/biotechnology/nih-guidelines/> and FAQs: <https://osp.od.nih.gov/biotechnology/faqs-on-ibc-administration/>)?

☐ Yes

If yes, your study may require Institutional Biosafety Committee Review. Please contact [[contact]](mailto:[contact]) for guidance.

☒ No

Optional comments:

N/A

**b. Data Analysis**

Describe the data analysis plan, including:

- Statistical procedures.

**Phase 2**

Statistical Design: The primary analysis for Aim 3 will be an intent-to-treat analysis using chi square tests and binomial regression. For the primary outcome, differences in the proportion of patients prescribed safer diabetes regimens (i.e., discontinuation of sulfonylureas, mealtime or mixed insulin) will be assessed at 6 months in the treatment vs. control arms. For the secondary outcomes, differences will be assessed in the proportion of patients who had an ED visit or hospitalization for hypoglycemia within 6 months, were prescribed CGM or prescribed glucagon, and were in glycemic control (HbA1c<8%) between the 2 study arms. The investigators will perform exploratory Heterogeneity of Treatment Effect (HTE) analyses for age, race and enrollment criterion (see above) by testing for statistical interactions with the exposure (treatment arm).

- When applicable, the power analysis.

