Severe hypoglycemia is the most common adverse drug effect associated with diabetes medications. However, hypoglycemia in patients with T2D is not adequately recognized, documented, or treated by care providers. Ever since landmark clinical trials (e.g., UKPDS) demonstrated that lowering blood glucose levels reduced the risk of long-term diabetes complications, the medical community has prioritized A1C reduction, often underestimating the risks of diabetes medications, especially hypoglycemia. Each year, approximately 11% of KPNC patients with type 2 diabetes experience severe hypoglycemia (a hypoglycemic episode requiring third-party assistance), with the risk increasing with age and duration of diabetes. (Karter, 2018) In older adults, approximately 13% of emergency department admissions for adverse drug events are due to hypoglycemia (primarily in insulin-treated

patients)(Shehab, 2016), and annual hospital admissions for hypoglycemia now surpass those for hyperglycemia.(Lipska, 2014)

The research question is whether an intervention by a hypoglycemia champion directed towards patients at high risk of hypoglycemia can reduce hypoglycemia events more than usual care (which will include a new treatment algorithm aimed at hypoglycemia risk reduction).

We previously developed a hypoglycemia risk tool which can stratify patients into low, intermediate or high risk for ED visit or hospitalization for hypoglycemia.(Karter, 2017; Karter, 2019) We demonstrated that patients classified as high risk for hypoglycemia were 35 times more likely to have an ED or hospital visit for hypoglycemia in the subsequent 12 months, compared to patients classified as low risk. However, it is important to note that ED or hospital visits for hypoglycemia are just the tip of the iceberg: 95% of patients experiencing severe hypoglycemia are cared for outside of the medical system (i.e., assisted by family or others).(Karter, 2018)

Currently, no well-validated, population management approach for hypoglycemia prevention exists. Front line clinicians need information and guidance on how to minimize hypoglycemia risk while optimizing glycemic control to reduce long-term diabetes complications. Thus, the development and evaluation of interventions to address hypoglycemia risk are needed and are highly relevant to TPMG care delivery, patient safety, and strategic goals of maintaining stellar HEDIS performance metrics.

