**Phase 2**

In **Phase 2** of this study (Aim 3), the investigators will:

- conduct a prospective evaluation of whether proactive intervention by the Hypoglycemia Champion (augmented usual care) is associated with better diabetes regimen safety among KPNC members at high risk of hypoglycemia compared to usual care (control) [Aim 3].

**Aim 3 –Conduct a prospective evaluation of whether proactive intervention by the Hypoglycemia Champion APM (i.e., assignment to augmented usual care group) is associated with better diabetes medication regimen safety among KPNC members at high risk of hypoglycemia compared to usual care (control).**

- Randomly assign eligible patients to receive proactive intervention by the HC APM (augmented usual care group) for comparison to data-only patients receiving usual care. All eligible patients will be managed according to the regionally disseminated HOAP as new standard of care). All medical decisions for all patients (augmented usual care and usual care) are made by each member’s medical care team responsible for his or her care (not by study personnel).
- **Primary Outcome:** Proportion of high-risk patients prescribed safer diabetes regimens (discontinuation at 6 months compared to pre-baseline of sulfonylureas, mealtime [rapid-/short-acting], or mixed insulin) comparing study participants (augmented usual care) to data-only patients (usual care controls). The study hypothesis is that more study participants will be prescribed safer diabetes regimens compared to data-only patients. Baseline pharmacy dispensing data and medication discontinuation orders during follow up will be collected directly from EHR/Clarity tables.
  - i. As researchers, patients will not be contacted directly at any time.
  - ii. All care will be delivered under approved protocols by KPNC clinicians.
  - iii. All evaluation data related to clinical outcomes will be collected directly from the medical record of usual care.
- **Secondary Outcomes:** the investigators will also examine differences between study participants and data-only patients in glucagon prescribing, CGM use, hypoglycemia on the

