**Phase 2**

Power Calculation: In preparation for this proposal, baseline use of hypoglycemia-prone medications (e.g., sulfonylureas, mealtime, or mixed insulin) was evaluated in 3921 KPNC patients identified as “high risk” by the KPNC hypoglycemia risk tool. Among these patients, 75% were on hypoglycemia-prone treatment. Approximately 60% of the intervention arm and 20% of the usual care arm will be prescribed safer diabetes regimens within 6 months compared

to baseline. The minimum number of subjects needed to detect this 40% absolute difference, assuming 90% power and a 10% attrition rate, is 86 patients (43 per arm). With an enrollment size of 200 (100 per arm), this trial is more than adequately powered to detect the hypothesized difference.

- Any procedures that will be used for quality control of collected data.

Data analysts routinely inspect the data for corrupt fields or extreme outliers.

c. Sharing of Results with Subjects

Describe whether results (study results or individual subject results, such as results of standard or research lab tests and genetic tests) will be shared with subjects or their providers and under which circumstances.

N/A

If the study carries a risk of incidental findings, describe your plan for evaluating these and determining whether and how subjects or their providers will be given this information.

N/A

If laboratory results will be shared with subjects or their healthcare providers, verify that the laboratory conducting the test is Clinical Laboratory Improvement Amendments (CLIA) certified.

N/A

Describe how study participants will be updated on research progress via newsletter, summary, etc. Consider incorporating such updates to study participants as part of ongoing retention efforts.

N/A

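### The only hypoglycemia event outcome is counted in the same 6 months in which drugs are being stopped, which dilutes a secondary comparison that 100 patients per arm already leave imprecise

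*Supplement*

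**What the plan says.** All references are to the version dated January 27, 2025.

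- **Section 3a, Scientific Background**, puts the research question in terms of events: whether the champion "can reduce hypoglycemia events more than usual care". Section 4 lists fewer ED visits or hospitalizations for hypoglycemia among its secondary hypotheses.
- **Section 9b, Statistical Design**, gives the only window for that outcome: "the proportion of patients who had an ED visit or hospitalization for hypoglycemia within 6 months". The analysis is intent-to-treat, by chi-square tests and binomial regression.
- **Section 4, primary outcome**, is "discontinuation at 6 months compared to pre-baseline of sulfonylureas, mealtime [rapid-/short-acting], or mixed insulin". The power calculation in section 9b assumes "Approximately 60% of the intervention arm and 20% of the usual care arm will be prescribed safer diabetes regimens within 6 months compared" to baseline.
- **Section 9a, Aim 3 chronology**, places identification of patients, random selection and baseline data in months 5-6, and outreach in months 7-12. For months 13-21 it says: "Collect outcome data from EMR for study participants and data-only patients".
- **Section 9a, duration**: "Participation in the study will end within 25 months after enrollment of first participant and no later than 01/31/2026". The same section gives 01/31/2026 both for the end of enrollment and for study completion.

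**The concern.** The champion is expected to reduce events mainly by getting hypoglycemia-prone drugs stopped. A stop counts towards the primary outcome whenever it occurs up to month 6, but it can prevent events only from then on. A patient whose drug is stopped in month 5 contributes about 5 months of unchanged exposure and 1 month of possible benefit to the event outcome. Because the event window closes when the regimen is assessed, the months in which the arms should differ most are not observed.

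The comparison is also small. The 100 per arm were sized for a 40-point difference in regimen change, not for events. A result close to no difference would be likely even if the primary hypothesis were true, and section 3a invites a reader to take that result as an answer to the question about events.

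**Working it through.** **The plan's own figure.** The only sample size stated is 43 per arm, for the primary outcome; none is given for events. For 60% vs 20% and 90% power, with two-sided 5% assumed because alpha is not stated:

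n = [1.96·√(2·0.4·0.6) + 1.2816·√(0.6·0.4 + 0.2·0.8)]² / 0.4² = (1.358 + 0.811)² / 0.16 = 29.4, so 30 per arm, and 30/0.9 gives 34 with 10% attrition.

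The stated 43 is not reproduced at that alpha, but it is conservative and has no bearing on this point.

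**How much of the window precedes the change.** Among patients who stop at month m after time zero, the share is m/6.

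- Clock from the end of month 6, outreach spread evenly over months 7-12: mean time to first contact is 3 months, so 3/6 = 50% of the window passes before contact.
- Clock from first contact, stop at 1 month: 1/6 = 17%.

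The protocol does not choose between these. Section 5b equates cohort baseline with enrollment in the cohort. Section 6 says data-only patients are not contacted, so they have no contact date. A clock common to both arms can therefore start only at cohort entry or allocation.

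**Effect on the rate ratio.** Assumptions: 60% and 20% are shares of the whole arm; the event rate is constant on the unchanged regimen and zero after stopping. Zero is generous, because insulin other than mealtime or mixed is not in the outcome. With f the average share of the window spent after stopping among those who stop, the ratio is (1 − 0.6f)/(1 − 0.2f).

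| Stop time (assumed) | Months 0-6 | Months 0-12 |
|---|---|---|
| Uniform over months 0-6 | f = 1/2: 0.70/0.90 = 0.78 | f = 3/4: 0.55/0.85 = 0.65 |
| Month 1 | f = 5/6: 0.50/0.833 = 0.60 | f = 11/12: 0.45/0.817 = 0.55 |
| At once | f = 1: 0.40/0.80 = 0.50 | f = 1: 0.50 |

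**Precision.** The protocol gives no event rate for this cohort. Section 3a allows a rough upper figure for patients the tool classes as high risk. About 11% of patients have severe hypoglycemia each year, and "95% of patients experiencing severe hypoglycemia are cared for outside of the medical system", so about 11% × 5% = 0.55% per year are seen in care. High-risk patients are "35 times more likely to have an ED or hospital visit for hypoglycemia in the subsequent 12 months" than low-risk patients, whose rate cannot exceed the overall rate. Hence at most 35 × 0.55% = 19.25% per year. I use this as an assumed rate and show 10% beside it. Counts are for 100 per arm with uniform stopping and no attrition; multiplier = exp(1.96·√(1/a + 1/b)).

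| Yearly rate (assumed) | Window | Events, control vs champion | Multiplier | 95% CI around the expected ratio |
|---|---|---|---|---|
| 19.25% | 0-6 | 8.7 vs 6.7 | 2.74 | 0.28 to 2.13 |
| 19.25% | 0-12 | 16.4 vs 10.6 | 2.17 | 0.30 to 1.40 |
| 19.25% | 6-12 | 7.7 vs 3.85 | 3.4 | 0.15 to 1.70 |
| 10% | 0-6 | 4.5 vs 3.5 | 4.0 | 0.19 to 3.1 |
| 10% | 0-12 | 8.5 vs 5.5 | 2.9 | 0.22 to 1.9 |

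**Cross-check on proportions.** Take an assumed 6-month risk of 10% on the unchanged regimen, full effect, and stopping at month 3. The 6-month window gives 9.0% vs 7.1% (2.0 points, power 7%); 12 months gives 16.2% vs 10.7% (5.6 points, power 21%). Over 6-month risks of 2% to 15%, risk cuts of 50% to 100% and stops at month 0, 1 or 3, power is 3% to 32% at 6 months and 4% to 56% at 12.

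**The case against.** The strongest reply has five parts.

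- **The 6-month comparison is valid.** Intent-to-treat from assignment estimates the effect of assignment over 6 months. Dilution weakens that effect but does not bias its estimate. The champion may also act through CGM use, which needs no drug to be stopped. This stands. A reader might infer that the trial cannot answer the events question at all; the documents do not support that.
- **The loss may be small.** The documents give neither stop dates nor a time zero, so it is not established that much of the window precedes the change. Nor is a 22% reduction the most the window could show: the same model gives 40% with stopping at month 1 and 50% with stopping at once. This also stands.
- **A longer window does not rescue the outcome.** The 12-month interval still spans 1, and months 6-12 alone are less precise than months 0-6 (3.4 against 2.7). This stands, and it limits what the change can claim.
- **Other figures in section 3a do not help.** The tool's 12-month horizon does not dictate an outcome horizon. The 95% cared for outside the medical system are missed whatever the window.
- **Events are secondary.** Aim 3 and the primary outcome concern regimen safety, and the sentence about events sits in the Background. That lowers the weight of the point, but section 4 still states fewer events as a hypothesis.

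What remains is the overlap itself, the absence of any later window and the undefined start of the clock.

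**Conclusion.** The point holds as dilution of a secondary outcome that is already imprecise. The event window coincides with the months in which discontinuation accrues. Depending on time zero and stop dates, from under 20% to about half of it is spent before the change among those who stop. With uniform stopping, full removal of risk and 60% vs 20%, a 12-month window moves the expected ratio from 0.78 to 0.65. At the assumed 19% rate it narrows the multiplier from about 2.7 to about 2.2. If stopping were immediate the ratio would not move, and the gain would be extra events only.

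The result stays inconclusive at both assumed rates, and no case tried reached 80% power. The main limit is 100 per arm. The 19% is a rough bound for tool-classified patients only. Section 5b also admits patients with a recent ED visit or hospitalization, to whom it need not apply.

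**What to change.** In sections 4 and 9b:

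1. Start the event clock at allocation in both arms and say so.
2. Keep the 6-month proportion. Add ED visits and hospitalizations for hypoglycemia from allocation to 12 months, censored at death, end of membership or end of data, as a person-time rate ratio with a 95% confidence interval.
3. Show months 6-12 descriptively only.
4. Present the event result as an estimate, not as a test of whether the champion reduces events.

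In section 3a, align the research-question sentence with the Aim 3 hypothesis on regimen safety.

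In section 9a, reconcile the enrollment-end and completion dates. With both at 01/31/2026, a late enrollee could have no follow-up, even for the 6-month outcomes. The 25-month limit does not settle this, because it runs from the first enrollment and is not follow-up per patient.

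**Cost.** Protocol wording and one longer EMR extract, with no added patients or contact. On the section 9a chronology, allocation in months 5-6 puts the 12-month point at about months 17-18, inside the month 13-21 collection. A clock starting at a first contact in month 12 would instead run to month 24, past the end of collection.

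**Downside.** Follow-up is unequal for late enrollees, and the added months include later care in both arms.
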